### Safety

The selected dosage and the exclusion criterion regarding additional selenium supplementation intake ensure that participants have a total selenium intake of less than 300 μg per day, as recommended in current European guidelines on tolerable upper intake level [46]. It has previously been concluded that SelenoPrecise^®^ is adequately characterized, of reproducible quality, and that there is no evidence of toxicity even at intake levels far above 300 μg per day [47]. In a randomized clinical trial (UK PRECISE) with 501 volunteer participants from general practice, mean plasma selenium increased from 88.1 μg/l to 188.1 μg/l following 6 months supplementation with 200 μg/day SelenoPrecise [48]. While no serious adverse events occurred, 12 adverse events were reported, primarily stomach or abdominal discomfort, which were equally distributed between the selenium and placebo groups [48]. The tablets used were identical to the planned experimental intervention agent in CATALYST, and CATALYST participants are expected to be very similar to the UK PRECISE participants, with regard to baseline selenium status.

The safety profile of the dietary supplement used in the CATALYST trial is based on the summary of product characteristics (SPC) for the drug formulation of SelenoPrecise^®^ from the Danish Medicines Agency. Common adverse reactions (between 1/10 and 1/100) are complaints from the gastrointestinal system, while uncommon (between 1/100 and 1/1,000) and rare (between 1/1,000 and 1/10,000) adverse reactions are mainly of a dermatological nature.

### Outcomes

Data will be collected for outcome assessment at six specified times during the trial (Table 1).

**Table 1 T1:** Timing of data collection

**Variable**	**Inclusion baseline**	**Follow-up 6 weeks ± 1 week**	**Follow-up 3 months ± 2 weeks**	**Follow-up 6 months ± 2 weeks**	**Follow-up 12 months ± 2 weeks**	**Follow-up 18 months ± 2 weeks**
Visit	*x*		*x*		*x*	*x*
Weight	*x*_ *v* _		*x*_ *v* _		*x*_ *v* _	*x*_ *v* _
Medical treatment	*x*_ *v* _		*x*_ *v* _		*x*_ *v* _	*x*_ *v* _
ThyPRO	*x*_ *r* _	*x*_ *r* _	*x*_ *r* _	*x*_ *r* _	*x*_ *r* _	*x*_ *r* _
TSH, FT4, FT3	*x*_ *s* _		*x*_ *s* _		*x*_ *s* _	*x*_ *s* _
TPO-Ab	*x*_ *s* _		*x*_ *s* _		*x*_ *s* _	*x*_ *s,* _
LT4 dosage	*x*_ *v* _		*x*_ *v* _		*x*_ *v* _	*x*_ *v* _
Immunological and oxidative stress biomarkers	*x*_ *s* _		*x*_ *s* _		*x*_ *s* _	*x*_ *s* _
Selenium	*x*_ *s* _		*x*_ *s* _		*x*_ *s* _	*x*_ *s* _
Creatinine/iodine ratio in spot urine	*x*_ *s* _					
Tablet count			*x*_ *v* _		*x*_ *v* _	
Consumption of additional selenium	*x*_ *v* _		*x*_ *v* _		*x*_ *v* _	*x*_ *v* _
Adverse reactions			*x*_ *v* _		*x*_ *v* _	*x*_ *v* _
Serious adverse reactions and events (SARs, SUSARs and SAEs)						*x*_ *p* _

All assessments must be made at the time points specified above. If not possible at the specified time, the assessment shall still be conducted, and the time of assessment shall be noted in the specified electronic case report form (eCRF). *x*_
*v*
_, analyzed via data obtained in eCRFs at trial visits, administered through the trial data management system (TDMS); *x*_
*r*
_, analyzed via patient-reported outcomes, administered through the TDMS; *x*_
*s*
_, analyzed in blood or urine samples obtained at trial visits; *x*_
*p*
_, analyzed via public national registries at the end of the trial.

#### **
*Primary outcome*
**

Improved thyroid-related quality of life during the 12 months intervention after randomization, as measured by one composite score from the ThyPRO questionnaire [49].

#### **
*Secondary outcomes*
**

Secondary outcome assessment is specified in Table 1. Forkhead Box P3 mRNA will be measured as an immunological biomarker, and urinary 8-oxo-2'-deoxyguanosine and 8-oxoguanine will be measured as oxidative stress biomarkers.

#### **
*Assessment of adverse reactions and events*
**

The latest version of the SPC shall at all times be used for the assessment of adverse reactions (ARs), which will be reported as a secondary trial outcome. Participants are questioned about ARs according to Table 1. In addition, participants are instructed to contact their trial contact person if they experience symptoms suggestive of ARs.

In the assessment and reporting of serious adverse reactions (SARs), serious unexpected serious adverse reaction (SUSARs) and serious adverse events (SAEs), data on hospital admissions and mortality will be obtained through national registries at the end of the trial. Also, participants are informed and instructed to contact their trial contact person if they are admitted to a hospital for selenium intoxication, experience a clinical picture indicative of selenium intoxication, or experience a clinical picture that is unexpected but suspected to be related to selenium intoxication. When a possible serious event (SAE, SAR or SUSAR) is identified, details will be sought from the patient’s medical record and through direct contact with the patient. Any SAE, SAR or SUSAR will be reported as an outcome measure.

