Analyses will be performed using SAS (SAS Institute Inc. ©, Cary, NC, USA), version 9.3 or later. All analyses will be intention-to-treat analyses performed blinded with the two intervention groups concealed as, for example, ‘A’ and ‘B’. Significance tests will be at the 5% level and two-sided. Table 2 shows, for each outcome, its priority, when it will be measured, the mathematical type of measure, and the analytical procedure to be used when analyzing the outcome values. The analytical procedures and handling of missing values are described next.

**Table 2 T2:** Outcome measures

**Outcome (priority)**	**Times of measurements**	**Mathematical type of quantity (analytical category)**
ThyPRO composite scale score (P)	Time sequence of six measurements^a^	Numerical (1 + 2)
ThyPRO hypothyroid symptoms (S)	Time sequence of six measurements^a^	Numerical (1 + 2)
ThyPRO goitre symptoms (S)	Time sequence of six measurements^a^	Numerical (1 + 2)
LT4 dosage (S)	Time sequence of four measurements^b^	Numerical (1 + 2)
Serum TPO-Ab (S)	Time sequence of four measurements^b^	Numerical (1 + 2)
Serum FT3/FT4 Ratio (S)	Time sequence of four measurements^b^	Numerical (1 + 2)
Plasma selenium (S)	Time sequence of four measurements^b^	Numerical (1 + 2)
Biomarkers of immunology and oxidative stress (S)	Time sequence of four measurements^b^	Numerical (1 + 2)
Adverse reactions (S)	End of trial	Rate (3)
Serious adverse events (S)	End of trial	Rate (3)

Outcomes with priorities, times of measurement and mathematical types of quantity with analytical categories. P, primary outcome measure; S, secondary outcome measure. Analytical categories 1 to 3 are defined in the main text. ^a^, includes five measurements relative to the reference time (6 weeks, 3 months, 6 months, 12 months and 18 months after randomization); ^b^, includes three measurements relative to the reference time (3 months, 12 months and 18 months after randomization).

#### **
*Analytical procedures*
**

Depending on the specific analytical category of each outcome measure, one or two of three types of regression analyses will be applied (Table 2).

#### **
*Analytical categories*
**

*Type 1* includes a continuous outcome measure (*y*) measured 3 to 6 times at 6 weeks, 3, 6, 12 or 18 months after randomization. It is viewed as a linear function of time (*t*). The model is:

*y* = *a* + *b***I* + *c***t* + *d***I***t*

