## Discussion

The data available from previous trials warrant further investigation, since a benefit from selenium supplementation is still unproven in patients with AIT. In previous trials of intervention with selenium in patients with AIT, effect on serum TPO-Ab concentration has been the primary outcome. Intervention durations of 3, 6, 9, and 12 months using different selenium formulations have shown positive effects on serum TPO-Ab concentrations. This trial will be the largest yet, with 472 participants, and the first to measure changes in quality of life, by ThyPRO, as the primary outcome. The sample size estimate does not take dropouts or off-trial use of selenium supplements into account. Plasma selenium concentrations will be measured to assess selenium intake during the trial. Importantly, utilizing the ThyPRO questionnaire will enable us to determine how selenium supplementation may affect specific aspects of thyroid-related quality of life in AIT patients. In assessing quality of life, the effect of levothyroxine alone will be taken into account by adjusting for TSH levels. Choosing a 12-month intervention period allows for a time sequence of five measurements. The 6-month postintervention follow-up period was added to assess sustained effects. This trial will also look into selenium’s mechanisms of action in AIT, by measuring biomarkers of immunological activity, and will be the first to evaluate whether selenium supplementation affects LT4 dosage. Dosage reduction is of clinical interest and discontinuation of LT4 would be of direct clinical relevance. An effect of selenium supplementation on LT4 dosage is conceivable, owing to upregulation of selenoproteins involved in thyroid hormone synthesis or thyrocyte protection.

Participants will be stratified for LT4 treatment duration of more or less than three months, corresponding to newly diagnosed and established patients, respectively. Participants in the newly diagnosed patient group will respond to LT4 treatment *per se*, in terms of restoration of euthyroidism, while the established patient group will not experience major fluctuation in the thyroid hormone levels during the study period. The stratification also allows an investigation of whether the newly diagnosed and established patient groups respond differently to selenium supplementation. This investigation will, however, be strictly exploratory, as it is likely to be underpowered.

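### No record of the gut and skin symptoms that define adverse reactions is scheduled before the first tablet; if complaints present at entry are counted, the adverse-reaction rate ratio is diluted

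*Protocol article*

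**What the plan says.** - **Schedule.** Under Assessment of adverse reactions and events, "Participants are questioned about ARs according to Table 1". In Table 1 the row "Adverse reactions" is marked for the 3-, 12- and 18-month visits and is blank at inclusion. A second route is open between visits: "participants are instructed to contact their trial contact person if they experience symptoms suggestive of ARs".
- **Definition.** The same section requires reactions to be judged against the current product characteristics and names them as a secondary outcome.
- **Which reactions.** The Safety section says: "Common adverse reactions (between 1/10 and 1/100) are complaints from the gastrointestinal system". The uncommon and rare "adverse reactions are mainly of a dermatological nature".
- **Entry visit.** The informed consent procedure includes a medical history. The article does not link it to the symptoms in the product characteristics, and it has no row of its own in Table 1.
- **Analysis.** Table 2 lists adverse reactions as a secondary outcome, an end-of-trial rate in analytical category 3. Type 3 is a Poisson model with log link and log period as offset. No baseline term is named, and nothing is said about onset, worsening or repeated reports.

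**The concern.** Gut and skin complaints are common without any tablet. To decide at month 3 whether such a complaint is a reaction, one needs to know whether it was there before the first tablet. The schedule does not provide for asking, so the assessor would depend on recall or on whatever the medical history recorded.

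Background complaints that enter the count add about the same amount to both arms. On the ratio scale this moves the estimate toward 1, and the extra variance costs power. For a tolerability outcome the costly error is a finding of no difference that is read as reassurance.

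The timing makes this more than a detail for later documents. Counting rules can be written in an analysis plan, but a symptom record not taken before treatment starts cannot be reconstructed.

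**Working it through.** **1. Arm size, from the plan's own calculation.** Inputs from the sample size section: difference 4 points, SD 20, five measurements, correlation 0.50, 80% power, two-sided 5%.

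SD of the mean of five = 20 × √((1 + 4 × 0.5)/5) = 15.49.
n per arm = 2 × (1.960 + 0.842)² × 15.49² / 4² = 235.5, so 236.

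The stated 236 per arm is reproduced and used below. The article gives no power figure for adverse reactions.

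**2. Dilution model.** Let b be the share with a complaint at entry, c the new-onset risk on placebo and c + e the new-onset risk on selenium. If every entry complaint is counted:

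p0 = b + (1 − b)c, p1 = b + (1 − b)(c + e), and p1 − p0 = (1 − b)e.

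Power = Φ[(p1 − p0 − 1.96·se0)/se1], where se0 is the pooled and se1 the unpooled standard error with 236 per arm. This test of proportions stands in for the planned Poisson model. The values of b, c and e are assumptions; the documents give no figure for b.

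**3. One case in full.** c = 5%, e = 5 points.
- b = 0: 5% v 10%, se0 = 0.0243, se1 = 0.0241. (0.050 − 1.96 × 0.02425)/0.0241 = 0.10, so power is 0.54.
- b = 10%: 14.5% v 19.0%, se0 = 0.0344, se1 = 0.0343. (0.045 − 1.96 × 0.0344)/0.0343 = −0.65, so power is 0.26.

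**4. Range.**

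| New-onset risk, placebo v selenium | Complaint at entry, all counted | Observed | Ratio | Difference (points) | Power |
|---|---|---|---|---|---|
| 5% v 10% | 0 | 5.0% v 10.0% | 2.00 | 5.0 | 54% |
| 5% v 10% | 10% | 14.5% v 19.0% | 1.31 | 4.5 | 26% |
| 5% v 10% | 20% | 24.0% v 28.0% | 1.17 | 4.0 | 17% |
| 1% v 6% | 0 | 1.0% v 6.0% | 6.00 | 5.0 | 84% |
| 1% v 6% | 5% | 6.0% v 10.7% | 1.80 | 4.8 | 46% |
| 1% v 6% | 10% | 10.9% v 15.4% | 1.41 | 4.5 | 30% |
| 1% v 6% | 20% | 20.8% v 24.8% | 1.19 | 4.0 | 18% |

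The ratio falls steeply and the difference much less. Most of the lost power comes from added variance. If no entry complaint is counted, the b = 0 rows apply and nothing is lost.

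**The case against.** - **Nothing says that entry complaints are counted.** A reader might infer from the blank baseline cell that every gut or skin complaint enters the count in both arms, perhaps once per visit. The documents do not support that. They speak of reactions, which cannot precede the first tablet, so a blank cell under that label is not an error in itself. Attribution or the entry medical history may remove some old complaints. Table 2 gives an end-of-trial rate without a rule on repeats. This objection stands, and the dilution is conditional.
- **Attribution and counting rules belong in other documents.** That is fair for the rules. It does not cover the collection schedule, which the article states outright.
- **The assumed rates are high.** The Safety section reports 12 adverse events among 501 participants taking the same tablet or placebo, about 2.4% if one per person, equally distributed between arms. The illustration has 14.5% to 24% of placebo participants reporting in the 5% rows, roughly 6 to 10 times as many. How that trial collected events is not stated, so the comparison is only indicative, but the power figures should be read as a sensitivity range.
- **Randomisation balances background complaints.** Correct. With blinding, this rules out a spurious difference between arms; what is lost is sensitivity.
- **Newly treated patients.** Half the sample is to come from patients on levothyroxine for under 3 months, and the Discussion says: "Participants in the newly diagnosed patient group will respond to LT4 treatment". A reader might expect a baseline record to deal with this. It would not: a symptom that changes after entry is still new or worse than at baseline. The placebo arm, with randomisation stratified by treatment duration, handles it.

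**Conclusion.** The point holds as a low-cost improvement to a named secondary safety outcome; the plan is not wrong as written. No entry record of the relevant symptoms is scheduled, and the article leaves open whether complaints present at entry count as reactions.

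If all are counted, the illustrated ratio falls from 2.0 to between 1.17 and 1.31, or from 6.0 to between 1.19 and 1.80, with power falling to between 17% and 46%. These sizes rest on assumed entry prevalence and new-onset risks, and on a proportions test in place of the Poisson model. Even without dilution, the 5% v 10% case has only about 54% power, so the fix would not by itself make a null result reassuring. The primary outcome is untouched, and so are serious events identified through registries.

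**What to change.** In Table 1, add an x_v in the inclusion-baseline column for the symptom questions based on the product characteristics, asked before the first tablet and in the same words as at follow-up. In the Type 3 analysis, state that only complaints that are new or worse than at baseline are counted, and that each continuing complaint is counted once. Show the count of all complaints as a supplementary table.

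The cost is a few minutes per participant at a visit that already takes place, one existing form used once more, and one sentence in the analysis text. Judging whether a complaint is worse than at baseline needs a simple graded answer.

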### Research biobank

A central research biobank, of buffy coat, serum, plasma and urine samples, will be established for analyses of biochemical markers specified in the outcome section and for future use. Future sample analyses include genome-wide association studies (regarding predictors of experimental intervention effect, or other predictors of autoimmunity) as may be specified in forthcoming protocols. Participants are informed orally and in writing, and will consent to the withdrawal and storing of biological material in the CATALYST trial. For this purpose, tubes of blood and urine will be collected at each of the four trial visits. Trained trial personnel will perform blood sampling; the risks involved with blood sampling are no more than with standard blood sampling.

### Monitoring

The trial will be monitored according to the International Committee of Harmonisation guidelines for good clinical research practice (ICH-GCP) by internal monitoring [50].

### Statistical analyses

#### **
*Primary outcome: sample size estimation*
**

The primary outcome is thyroid-related quality of life during 12 months’ intervention, as measured by a composite score from the ThyPRO questionnaire. Sample size estimation is based on this outcome.

The trial should be sufficiently powered to identify a difference between the intervention and the control group of four points on the 0 to 100 ThyPRO composite scale, corresponding to a small to moderate effect. In previously obtained data, the standard deviation of ThyPRO-scores (sigma level) was 20 points [14]. With a correlation between observations on the same participant of 0.50, and a power of 80% and a type I error probability (two-sided α level) of 0.05, a sample size of 236 experimental participants and 236 control participants is required. The sample size estimate is based on a design with five repeated measurements having a compound symmetry covariance structure [51].

#### **
*Secondary outcomes: power estimation*
**

Power calculations are based on serum TPO-Ab concentrations and LT4 dosage. Standard deviations used for power calculations were extracted from unpublished data in a study population of approximately 200 AIT patients from Copenhagen and Odense University Hospitals receiving LT4 treatment [14].

#### **
*Serum TPO-Ab concentration*
**

While a previous study has linked TPO-Ab positivity in hypothyroid patients to impaired HRQL [20], we have not found conclusive evidence in the literature that the level of serum TPO-Ab among participants in this trial, that is, AIT patients with serum TPO-Ab concentration ≥100 IU/ml, has clinical implications. The power estimate is based on a design with three repeated measurements having a compound symmetry covariance structure, with a standard deviation (σ level) of 535 IU/ml (unpublished data) [14], a correlation between observations on the same participant of 0.50, and a type I error probability (two-sided α level) of 0.05. Under these circumstances, a difference in serum TPO-Ab levels of 138 IU/ml between the experimental and control group can be identified with 80% power. We find the power of the trial to assess effect on serum TPO-Ab concentrations acceptable.

#### **
*LT4 dosage*
**

In this trial, a difference in LT4 dosage of 25 μg/day between the experimental and control group following intervention should be detected, since 25 μg/day is a minimal dosage adjustment readily made by clinicians, when patients are treated with the most common LT4 formulation (Eltroxin) on the Danish market. The power estimate is based on a design with five repeated measurements having a compound symmetry covariance structure, with a standard deviation (σ level) of 81 μg/day (unpublished data) [14], a correlation between observations on the same participant of 0.50, and a type I error probability (two-sided α level) of 0.05. Under these circumstances, the probability (power) of finding a true difference in LT4 dosage of 25 μg/day between the experimental and control group following intervention is 92%, which we find acceptable.

#### **
*Expected participant recruitment*
**

The patient uptake areas for the participating clinical trial sites comprise a total of 910,000 persons (Rigshospitalet: 70,000; Odense University Hospital: 350,000; Bispebjerg Hospital: 270,000; Hospital of Southwest Denmark (Esbjerg): 220,000).

Previous studies report an incidence of 40 per 100,000 per year of spontaneous (presumed autoimmune) hypothyroidism after the implementation of iodine fortification in Denmark [5,6]. This corresponds to 364 patients per year in the given uptake area. A considerable proportion of hypothyroid patients are treated in the primary care sector, and will neither be referred to nor followed at a participating clinical trial site. Assuming an inclusion of 30% of the annual incident patients, we will be able to include 109 participants per year or nine participants per month. Half of the 472 participants will be included from the incident (LT4 treatment <3 months) group, and this is expected to take 24 to 26 months. In addition to this, established patients (LT4 treatment ≥ 3 months) with autoimmune thyroiditis are eligible for inclusion. The prevalence of diagnosed and treated hypothyroidism was 1% in a previous iodine fortification program (DanThyr) with a population of 4,073 men and women. 83% of hypothyroid patients had serum-TPO-Ab above 200 IU/ml [5]. An estimated AIT prevalence of 1% among adults in our patient uptake area will be approximately 10,000 individuals. We expect to recruit 236 participants from the prevalent patient group within the 24 to 26 month recruitment period of the incident patients.

#### **
*Data analyses*
**

Analyses will be performed using SAS (SAS Institute Inc. ©, Cary, NC, USA), version 9.3 or later. All analyses will be intention-to-treat analyses performed blinded with the two intervention groups concealed as, for example, ‘A’ and ‘B’. Significance tests will be at the 5% level and two-sided. Table 2 shows, for each outcome, its priority, when it will be measured, the mathematical type of measure, and the analytical procedure to be used when analyzing the outcome values. The analytical procedures and handling of missing values are described next.

**Table 2 T2:** Outcome measures

**Outcome (priority)**	**Times of measurements**	**Mathematical type of quantity (analytical category)**
ThyPRO composite scale score (P)	Time sequence of six measurements^a^	Numerical (1 + 2)
ThyPRO hypothyroid symptoms (S)	Time sequence of six measurements^a^	Numerical (1 + 2)
ThyPRO goitre symptoms (S)	Time sequence of six measurements^a^	Numerical (1 + 2)
LT4 dosage (S)	Time sequence of four measurements^b^	Numerical (1 + 2)
Serum TPO-Ab (S)	Time sequence of four measurements^b^	Numerical (1 + 2)
Serum FT3/FT4 Ratio (S)	Time sequence of four measurements^b^	Numerical (1 + 2)
Plasma selenium (S)	Time sequence of four measurements^b^	Numerical (1 + 2)
Biomarkers of immunology and oxidative stress (S)	Time sequence of four measurements^b^	Numerical (1 + 2)
Adverse reactions (S)	End of trial	Rate (3)
Serious adverse events (S)	End of trial	Rate (3)

Outcomes with priorities, times of measurement and mathematical types of quantity with analytical categories. P, primary outcome measure; S, secondary outcome measure. Analytical categories 1 to 3 are defined in the main text. ^a^, includes five measurements relative to the reference time (6 weeks, 3 months, 6 months, 12 months and 18 months after randomization); ^b^, includes three measurements relative to the reference time (3 months, 12 months and 18 months after randomization).

#### **
*Analytical procedures*
**

Depending on the specific analytical category of each outcome measure, one or two of three types of regression analyses will be applied (Table 2).

#### **
*Analytical categories*
**

*Type 1* includes a continuous outcome measure (*y*) measured 3 to 6 times at 6 weeks, 3, 6, 12 or 18 months after randomization. It is viewed as a linear function of time (*t*). The model is:

*y* = *a* + *b***I* + *c***t* + *d***I***t*

Depending on the mean value structure in the two groups, this model may be enhanced to include a second- or third-degree polynomial. *I* is the intervention indicator, and *a*, *b*, *c* and *d* are the coefficients of the regression equation. A mixed model with repeated measures will be used. An unstructured covariance matrix will be used. In the case of lack of convergence, the following covariance structures will be tried in the specified order: the spatial power law and the compound symmetric.

*Type 2* includes a single continuous outcome measure. The general linear univariate model will be used. As a sensitivity analysis, a nonparametric test (Mann Whitney) will be conducted and the result discussed.

*Type 3* includes a count of events within a specified period of counting as outcome measure. The generalized linear model will be used with the Poisson distribution, link = log and log (period) as offset. As a sensitivity analysis a nonparametric test (Mann Whitney) is conducted to compare the distributions of rates between the groups and the result discussed.

#### **
*Missing values*
**

If the distributions of the primary outcome measure differ significantly between the two intervention groups, multiple imputations (MI) will be used to replace missing data with substituted values using SAS version 9.3 or later. In the MI analysis, the model variables and additional variables significantly related to the variables with missing values of these variables will be used. Ten imputed data sets will be produced.

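### The sample size counts five ThyPRO scores for a 12-month outcome that has four post-randomisation scores, and no primary contrast is tied to the power figure

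*Protocol article*

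**What the plan says.** The sample size paragraph (Protocol article, Statistical analyses) fixes the period: "The primary outcome is thyroid-related quality of life during 12 months’ intervention". It targets "a difference between the intervention and the control group of four points on the 0 to 100 ThyPRO composite scale", and its other inputs are that "the standard deviation of ThyPRO-scores (sigma level) was 20 points" and "With a correlation between observations on the same participant of 0.50", with 80% power and two-sided alpha 0.05. It arrives at 236 per group and adds: "The sample size estimate is based on a design with five repeated measurements having a compound symmetry covariance structure".

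The article accounts for the number five in two ways:

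- Discussion: "Choosing a 12-month intervention period allows for a time sequence of five measurements". In Table 1, five scores up to 12 months are found only if baseline is one of them.
- Table 2, footnote a: the five are 6 weeks, 3, 6, 12 and 18 months after randomisation. The Discussion describes the six months after month 12 as follow-up after the intervention, meant to look for lasting effects.

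For the analysis, Type 1 says of the outcome: "It is viewed as a linear function of time". The printed model has an intercept, a group term I (coefficient b), a time term t (coefficient c) and their product I×t (coefficient d), with an option to add polynomial terms. No coefficient or contrast is named as the primary test. On attrition the Discussion is open: "The sample size estimate does not take dropouts or off-trial use of selenium supplements into account".

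**The concern.** A sample size built on repeated measurements gains precision from each score that carries the treatment effect. A baseline score carries none, because the groups have not yet been treated. An 18-month score lies outside the stated outcome period. If neither belongs, the calculation credits one measurement too many, and no dropout allowance is there to absorb the difference.

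The second matter is the link between the power figure and the test. The calculation concerns a difference averaged over time. The printed model yields several quantities: a group difference at time zero, a slope difference, and any weighted combination of the two. Their power differs widely. Unless the deciding contrast is named, a reader cannot tell which test the 80% describes, and the choice could be made after the profiles over time have been seen.

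**Working it through.** **Inputs** (sample size paragraph): difference δ = 4, SD σ = 20 (σ² = 400), within-participant correlation ρ = 0.50, z-values 1.96 and 0.8416, 1:1 allocation, no dropout. Schedule from Table 1.

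**Formulas.** Under compound symmetry the mean of m scores has variance σ²·f(m), with f(m) = (1 + (m − 1)ρ)/m. Then n per group = 2(1.96 + 0.8416)²·σ²·f(m)/δ², SE = √(2σ²·f(m)/n), and power ≈ Φ(δ/SE − 1.96).

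**1. The protocol's figure, m = 5.** f = 3/5 = 0.600, variance 240. n = 2 × 7.849 × 240/16 = 235.5, so 236. At 236: SE = √(480/236) = 1.426, 4/1.426 = 2.805, power 80.1%. The stated figure is reproduced, as an unadjusted comparison of time-averaged means.

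**2. Four scores in the outcome period, m = 4.** f = 2.5/4 = 0.625, variance 250. n = 2 × 7.849 × 250/16 = 245.3, so 246 (10 more per group, 4.2%). At 236: SE = √(500/236) = 1.456, 4/1.456 = 2.748, power 78.5%.

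**3. Four scores with baseline as a covariate.** Baseline has correlation 0.50 with each later score, so the variance factor falls by ρ²: 0.625 − 0.25 = 0.375, variance 150. n = 2 × 7.849 × 150/16 = 147.2, so 148. At 236: SE = √(300/236) = 1.127, 4/1.127 = 3.548, power 94.4%.

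**4. Can the printed model deliver the average?** Yes. The average difference is b + d·t̄, where t̄ = (1.5 + 3 + 6 + 12)/4 = 5.625 months. Under compound symmetry and complete data its SE is the 1.456 of step 2, so its power is again 78.5%.

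**5. Single coefficients, four post-randomisation scores, 236 per group.** The squared deviations of the times from t̄ sum to 64.69. SE(d) = √(2 × 400 × 0.5/(236 × 64.69)) = 0.162 and SE(b) = √(1.456² + 5.625² × 0.162²) = 1.717.

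| Assumed effect | Test of b | Test of d | Average |
|---|---|---|---|
| Constant 4 points | 64% | 5% | 78.5% |
| Linear growth to 4 points at 12 months | 5% | 54% | 25% |

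The last cell uses a mean effect of 4 × 5.625/12 = 1.875 points: 1.875/1.456 = 1.288, power Φ(−0.672) = 25%. The effect shapes are assumptions; the protocol states none beyond the single 4-point difference.

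**6. Dropout (assumed 10% and 20%, complete-case count).** With 212.4 and 188.8 per group, the unadjusted four-score average has 74% and 69% power. The baseline-adjusted average has 92% and 89%.

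**The case against.** The sample size paragraph speaks of repeated measurements without saying that all five fall on treatment, and footnote a does list exactly five post-randomisation scores. That is fair, but the same paragraph confines the outcome to the 12-month intervention, and the Discussion explains the five by that same period. The two accounts cannot both hold, and neither yields five post-randomisation scores within it.

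The count error is minor: 1.6 percentage points of power, or 10 participants per group. That stands in full. The absence of a dropout allowance is openly declared and is not itself an error.

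A reader might infer that the linear model cannot test the average, or that 80% power is lost. The document supports neither. The average is an estimable contrast of that model (step 4), and no passage says that b or d alone decides the trial. Table 2 also assigns the primary outcome a second procedure, Type 2.

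Other low figures invite the same mistake. Averaging baseline in as a fifth score would dilute 4 points to 3.2 and give 61% power (3.2/1.426 = 2.244), but no passage specifies that analysis.

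Nor does the article rule out baseline adjustment. The printed equation is evidently not exhaustive, since the Discussion promises adjustment for TSH and the equation has no TSH term. Baseline adjustment is therefore an available improvement, not the correction of a proven omission.

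**Conclusion.** The point holds at moderate severity. On the protocol's own inputs, 236 per group gives 78.5% power for the unadjusted average of the four scores in the outcome period, and 246 would be needed for 80%. Taken alone, the miscount would hardly matter. It matters together with two incompatible accounts of what the five scores are and with a power figure not tied to any named test.

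The 80% is thus not established for a stated analysis, which is different from saying that it is not achieved. With the average as contrast the trial has close to its stated power, and well above it with baseline as a covariate. For the constant difference that the calculation assumes, a test of either coefficient alone would have less. For an effect that builds over time, the ranking can change.

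All figures assume SD 20, compound symmetry with correlation 0.50 (including between baseline and later scores), and complete data unless dropout is stated.

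**What to change.** - Reconcile the count in the sample size paragraph, Table 2 footnote a and the Discussion. State that the primary outcome uses four post-randomisation scores (6 weeks, 3, 6 and 12 months) and that the 18-month score serves the follow-up question only.
- Name the primary contrast: the average selenium–placebo difference over 6 weeks to 12 months, from the mixed model, with baseline ThyPRO as a covariate.
- Restate power at 236 per group as about 78.5% unadjusted and about 94% baseline-adjusted (148 per group would suffice for 80%), and add the figure under a declared dropout assumption.
- Keep 472 participants.

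The cost is a few sentences, with no added patients or visits, since baseline ThyPRO is already collected. The unadjusted figure becomes slightly less favourable. There is one trade-off to accept knowingly: an average over the whole period is less sensitive than a slope or late-time contrast if the effect emerges only gradually (step 5), so the choice should be made and recorded before unblinded results are seen.
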